## Methods: participants, interventions, and outcomes

### Study setting {9}

This study will be conducted at:IVFHK-CUHK, the leading in vitro fertilization (IVF) center of this trial. The center situates in the Prince of Wales Hospital (PWH) and operates under the Department of Obstetrics and Gynaecology at The Chinese University of Hong Kong (CUHK).CUHK Medical Centre (CUHKMC), a private IVF center in Hong Kong under the Faculty of Medicine, The Chinese University of Hong Kong.HEAL Fertility, a private IVF center in Hong Kong.

Other IVF centers may be allowed to join this trial.

Participants for the study will be recruited from patients undergoing FET cycles at these sites. Detailed information will be provided verbally and through consent forms, with eligibility criteria checked before inclusion in the study. Recruitment will be managed by the IVF research team and clinical team at PWH. Data collection will occur only at this site, and no international sites are involved in this local trial.

### Eligibility criteria {10}

#### Inclusion criteria

Participants will be eligible for inclusion in this study if they meet the following criteria:Patients undergoing a FET cycle at one of the study centers.Plan to undergo single embryo transfer (SET) during the FET cycle.Age between 18 and 45 years.Patients with at least one good-quality blastocyst suitable for transfer.Patients who have provided informed consent to participate in the study.

#### Exclusion criteria

Patients will be excluded from the study if they meet any of the following criteria:Patients with repeated implantation failure (RIF) or recurrent miscarriage (RM).Patients with known uterine anomalies or significant uterine pathology (e.g., fibroids, polyps).Patients who are unwilling or unable to provide informed consent.

### Who will take informed consent? {26a}

The informed consent for this trial will be conducted by a designated research assistant, nurse, or clinician at any of the participating study sites. The research assistant will be responsible for providing potential participants with comprehensive information regarding the study. This will include an explanation of the study’s purpose, procedures, potential risks, and benefits, as well as the rights of participants.

### Additional consent provisions for collection and use of participant data and biological specimens {26b}

There is no collection of biological specimens planned, and thus no additional consent will be required for biological samples.

## Interventions

### Explanation for the choice of comparators {6b}

In this trial, the comparator chosen is the conventional multi-step warming method, which is the current standard of care for thawing vitrified embryos in ART procedures [12]. This method has been widely used in clinical practice due to its established safety and effectiveness, making it an appropriate comparator for evaluating the new direct warming method.

The conventional multi-step method involves a series of steps that gradually remove cryoprotectants and rehydrate the embryo, ensuring its post-thaw survival. It typically requires 15–20 min to complete and is performed by trained embryologists. Despite its widespread use, the multi-step process is time-consuming and can incur significant costs, making it a useful benchmark for comparison with the new direct warming method, which aims to simplify the procedure and reduce both time and cost while maintaining or improving clinical outcomes.

The choice of this comparator allows the study to directly assess whether the new direct warming method can offer a more efficient and cost-effective alternative without compromising the success rates of embryo survival, implantation, pregnancy, and live birth.

### Intervention description {11a}

Intervention group (arm 1): new direct warming methodIn the intervention group, vitrified blastocysts will be thawed using a novel direct warming method. The ready-to-be-thawed blastocyst is placed in a pre-warmed direct warming medium for 1 min. Following this, the embryo is transferred directly into the embryo culture medium in a time-lapse system until it is ready for transfer into the uterus. This new warming method significantly reduces the procedure time to approximately 3 min, making it much faster than the conventional multi-step warming process.Control group (arm 2): conventional multi-step warming methodThe control group will follow the conventional multi-step warming method. In this procedure, vitrified embryos are first placed in a pre-warmed thawing solution for 1–3 min. They are then transferred to a dilution solution for 4–6 min to gradually dilute the cryoprotectants, followed by immersion in a washing solution for 5–10 min to complete the rehydration process. This multi-step method takes approximately 20 min to complete. After thawing, the embryos are placed in the embryo culture medium in a time-lapse system until they are ready for transfer.Blastocysts will be evaluated using the Gardner grading scale with a three-part criterion on blastocyst expansion, inner cell mass (ICM), and trophectoderm (TE) quality. Blastocysts with a score ≥3BB are considered good quality [13].

### Criteria for discontinuing or modifying allocated interventions {11b}

Participant request:If a participant requests to withdraw from the study at any time, their allocated intervention will be discontinued. The participant will be informed that they may withdraw without any negative consequences, and their withdrawal will not affect their future clinical care.Medical conditions:Should a participant’s medical condition change during the trial (e.g., significant changes in uterine health, onset of illness that may affect pregnancy outcomes), the intervention may be modified or discontinued in consultation with the participant and the study’s clinical team.Safety concerns:If any safety concerns arise during the embryo warming or transfer process, such as adverse reactions or unforeseen complications affecting the embryo’s viability or the participant’s health, the intervention may be halted. The trial’s clinical staff will monitor participants closely and stop the procedure if it is deemed unsafe to continue.

### Strategies to improve adherence to interventions {11c}

Training and standardization:All embryologists and clinical staff involved in the intervention and control procedures will receive detailed training on the standardized protocols for both the conventional multi-step warming method and the new direct warming method. This will ensure that all procedures are carried out consistently across participants and in line with the trial protocol.Regular monitoring:A dedicated Trial Monitoring Team will be established to observe and ensure protocol adherence throughout the trial. They will periodically review the warming and embryo transfer procedures, both in the intervention and control groups, to identify any deviations from the protocol.Documentation of procedures:For every participant, a detailed record of the warming process will be maintained, documenting the exact steps, time taken, and any deviations from the protocol. This will allow for tracking of adherence and enable prompt corrective actions if any protocol deviations are noted.Adherence audits:Routine audits will be conducted at regular intervals to review all aspects of the trial, including adherence to intervention protocols. These audits will ensure that any potential issues in protocol adherence are identified early and addressed.Participant engagement:Participants will be closely monitored for any concerns or discomfort during the procedure. Regular follow-ups will be scheduled. Any issues will be addressed by the clinical team immediately.By implementing these strategies, the trial aims to ensure high adherence to both the intervention and control protocols while minimizing variability in the procedures administered across the study.

### Relevant concomitant care permitted or prohibited during the trial {11d}

#### Permitted concomitant care

Standard fertility treatments:Participants may continue with standard fertility treatments such as hormonal support (e.g., progesterone, estrogen) as part of their IVF protocols. These treatments are necessary to maintain the optimal environment for embryo implantation and pregnancy support. The handling clinician will determine suitable treatment for the patients.Routine medications:Participants can continue any routine medications for pre-existing conditions (e.g., medications for asthma or mild allergies), provided these do not interfere with the study outcomes. The use of such medications will be documented for each participant.Follow-up appointments:Regular follow-up visits, including ultrasound scans and blood tests, are part of routine IVF care and will be permitted as part of the standard treatment plan.

#### Prohibited interventions

Experimental fertility treatments:Any unapproved or experimental fertility treatments or medications that are not part of the standard IVF protocol will be prohibited during the trial.Unapproved medications or supplements:Participants will not be allowed to take any fertility-related medications or supplements (e.g., herbal remedies, unapproved hormonal therapies) that are not prescribed by their reproductive specialist as part of the trial.Other assisted reproductive procedures:Participants will be prohibited from undergoing any additional assisted reproductive procedures (e.g., intrauterine insemination, gamete donation) outside of the planned embryo transfer during the trial.All concomitant care and interventions will be closely monitored, and any deviations from the allowed procedures will be documented. The trial’s clinical team will review these cases to assess any potential impact on the study outcomes.

### Provisions for post-trial care {30}

#### Ancillary and post-trial care

Participants will continue to receive routine clinical care as part of their standard fertility treatment at the PWH following their participation in this trial. This includes all necessary follow-up visits to monitor pregnancy outcomes and any standard care associated with IVF or embryo transfer. If any minor adverse events or complications related to the embryo warming process are encountered, appropriate medical care will be provided by the clinical team at no additional cost to the participant.

It is important to note that the most severe outcome related to embryo warming in this trial is likely to be the early cessation of embryo development, which may affect the overall pregnancy success rate. Studies have shown that miscarriage rates after FET are generally comparable to those with fresh transfers, provided the thawed embryo is healthy and viable [14, 15]. Furthermore, other ultra-fast warming methods have not shown an increased risk of miscarriage or adverse effects on pregnancy outcomes [7, 8]. No major clinical events, such as miscarriage or significant health complications, are expected to result directly from the embryo warming process, as warming itself does not significantly increase the risk of miscarriage.

#### Compensation for harm

Given the low-risk nature of the embryo warming procedure, particularly in relation to the embryo’s viability and pregnancy success rates, the likelihood of serious harm to participants is extremely low. However, in the unlikely event that a participant experiences an adverse event directly caused by the procedures involved in the trial, the study has comprehensive insurance coverage in place to provide compensation.

Participants will be informed during the informed consent process that they will not receive monetary compensation for participation in the trial itself. However, any medical costs related to adverse events caused by trial-related procedures will be fully covered by the study’s insurance policy. This ensures that participants are protected and that any necessary medical care will be provided at no cost to them.

### Outcomes {12}

#### Primary outcomes

The primary outcome of this study is to evaluate the clinical efficacy of the new direct warming method for FET compared to the conventional multi-step warming method. The key measures for the primary outcome include:Clinical pregnancy rate: defined as the presence of at least one intrauterine gestational sac detected via ultrasound at 6–8 weeks of gestation. Multiple pregnancies (two or more gestational sacs) are counted as one clinical pregnancy.Ongoing pregnancy rate: defined as the proportion of pregnancies that progress beyond 6–8 weeks, with at least one viable fetus with a heartbeat confirmed via ultrasound.Live birth rate: the proportion of participants who achieve a live birth, defined as the delivery of a live baby after 24 weeks of gestation.Miscarriage rate: the proportion of pregnancies resulting in pregnancy loss after the confirmation of clinical pregnancy.Cost-effectiveness: an evaluation of the cost savings achieved by using the new method, including reductions in time, materials, and labor compared to the conventional method.The equation for consumable cost: (total consumable cost of conventional warming in all centers/total cycle number of the conventional warming in all centers)/(total consumable cost of direct warming in all centers/total cycle number of the direct warming in all centers) × 100%.The equation for time cost: (total minutes spent on conventional warming in all centers/total cycle number of the conventional warming in all centers)/(total minutes spent on direct warming in all centers/total cycle number of the direct warming in all centers) × 100%.The equation for labor cost: (total hours spent on conventional warming in all centers/total cycle number of the conventional warming in all centers * role-specific hourly rates)/(total hours spent on direct warming in all centers/total cycle number of the direct warming in all centers * role-specific hourly rates) × 100%.

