**Fig. 1 Fig1:**
[figure not shown]
RCT flowchart

**Table 1 Tab1:** Schedule of the study process

Timepoint	Study period							
	Enrollment	Allocation	Post-allocation					Close-out
	IVF talk	0 week	Embryo transfer	10–14 days	6–8 weeks	20–24 weeks	36–40 weeks	6–8 weeks after birth
Enrollment								
Eligibility screen	X							
Informed consent	X							
Allocation		X						
Interventions								
Administration of different embryo warming methods			X					
Assessments								
Post-thaw embryo assessment			X					
HCG test				X				
Ultrasound of gestation					X			
Phone follow-up						X	X	X

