## Statistical methods

### Statistical methods for primary and secondary outcomes {20a}

All analyses will follow an intention-to-treat (ITT) approach, with statistical significance set at *p* < 0.05 and 95% confidence intervals (CI). Primary outcomes, including embryo survival rate, pregnancy rate, clinical pregnancy rate, and live birth rate, will be analyzed using logistic regression models, adjusting for potential confounders such as cause of infertility, previous ART cycle, and embryo quality. Chi-square tests or Fisher’s exact tests will be used for categorical outcomes like embryo survival, and logistic regression will report odds ratios (OR) for pregnancy and live birth rates.

Secondary outcomes, including implantation rate and multiple gestation pregnancy rate, will be analyzed using generalized linear models (GLM) and chi-square tests. Thawing time will be compared using *t*-tests or Mann-Whitney *U* tests for non-normal data. Cost-effectiveness will be evaluated through cost-effectiveness analysis (CEA), while post-thaw embryo quality will be assessed using standard grading criteria and analyzed with chi-square tests. Missing data will be handled using multiple imputation to maintain the integrity of the results. An extra sensitivity analysis will be conducted if loss to follow-up is more than 5%.

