### Methods in analysis to handle protocol non-adherence and any statistical methods to handle missing data {20c}

The primary analysis will be conducted on an ITT basis, which includes all participants as randomized, regardless of protocol adherence or deviations. Participants who discontinue the intervention will still be analyzed in the group to which they were originally assigned to preserve the randomization process.

To address potential missing data, multiple imputation techniques will be employed. Missing values will be imputed based on available baseline and follow-up data, ensuring that the analysis maintains sufficient statistical power. Sensitivity analyses will also be performed to assess the robustness of the results, comparing complete case analyses to those using imputed data.

Per-protocol analyses may also be conducted as a secondary analysis to assess the outcomes among participants who fully adhered to the study protocol.

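### Ongoing pregnancy and miscarriage are primary outcomes counted per pregnancy, against the intention-to-treat promise, and ongoing pregnancy has no scheduled scan of its own

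*Protocol article*

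**What the plan says.** All places are in the Protocol article.

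- **Primary outcomes, under Outcomes {12}.** Ongoing pregnancy is "defined as the proportion of pregnancies that progress beyond 6–8 weeks, with at least one viable fetus with a heartbeat", which ultrasound must confirm. Miscarriage is "the proportion of pregnancies resulting in pregnancy loss after the confirmation of clinical pregnancy". Live birth, in the same list, is "the proportion of participants who achieve a live birth". Clinical pregnancy is "the presence of at least one intrauterine gestational sac detected via ultrasound at 6–8 weeks of gestation", with no denominator given. The Abstract also lists all four as primary, with cost-effectiveness.
- **Analysis population, {20c}.** "The primary analysis will be conducted on an ITT basis, which includes all participants as randomized". Section {20a} likewise applies intention-to-treat to all analyses. The primary outcomes it names for modelling include neither ongoing pregnancy nor miscarriage, so it does not amend their denominators.
- **Schedule, Table 1.** The row "Ultrasound of gestation" has one mark, at 6–8 weeks. Contacts at 20–24 weeks, 36–40 weeks and after birth are by phone. The retention section {18b} gives the same sequence.
- **Concomitant care {11d}.** Scans in routine care are permitted, but no week is fixed and they are not tied to any outcome.

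**The concern.** An outcome whose denominator is pregnancies cannot include everyone randomised, so two of the five primary outcomes cannot be analysed as {20c} promises. The conflict is between statements in the article itself.

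It matters because the intervention acts before the denominator is formed. The post-trial care section {30} names arrest of the embryo as the likely worst consequence of warming and accepts that this could lower the chance of pregnancy. If the method changes who becomes pregnant, the two groups of pregnancies may differ in ways that randomisation no longer balances. A method could then look better or worse on these outcomes because of who entered the denominator.

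The timing of ongoing pregnancy is a second, separate defect. Its definition asks for ultrasound evidence later than the only scan the study schedules.

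**Working it through.** **The plan's own figure.** Sample size {14} gives 275 per arm, and 275 × 1.05 = 288.75, rounded to 289, so 2 × 289 = 578 as stated. The article gives no figure for ongoing pregnancy or miscarriage and no control rate for any outcome. All rates below are therefore assumptions, chosen to show the mechanism.

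**Notation.** Let c be clinical pregnancy per randomised participant and m the share of clinical pregnancies later lost. Per pregnancy, continuing is 1 − m and miscarriage is m. Per participant, continuing is c(1 − m) and miscarriage is c × m. Pregnancies are taken as clinical pregnancies; the ongoing pregnancy definition does not say whether it means these or positive hCG tests.

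**Example A: a worse method looks better.**

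| | Conventional | Direct |
|---|---|---|
| c (assumed) | 50% | 40% |
| m (assumed) | 20% | 15% |
| Continuing per pregnancy | 80% | 85% |
| Continuing per participant | 0.50 × 0.80 = 40% | 0.40 × 0.85 = 34% |
| Miscarriage per pregnancy | 20% | 15% |
| Miscarriage per participant | 0.50 × 0.20 = 10% | 0.40 × 0.15 = 6% |

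With these loss rates the two measures disagree whenever direct c is below 0.50 × 0.80 / 0.85 = 47.1%. A fall of about 3 points is enough.

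**Example B: a better method looks no better, or worse.** Assume conventional c = 45% and m = 15%. Direct warming keeps those pregnancies and adds 5 points of further ones, of which a share r is lost. Conventional continuing is 85% per pregnancy and 0.45 × 0.85 = 38.25% per participant.

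| r (assumed) | Direct m = (0.45 × 0.15 + 0.05 × r) / 0.50 | Direct continuing per pregnancy | Direct continuing per participant |
|---|---|---|---|
| 15% | 15.0% | 85.0% | 42.5% |
| 30% | 16.5% | 83.5% | 41.75% |
| 50% | 18.5% | 81.5% | 40.75% |

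Direct warming is better per participant in every row, yet equal or worse per pregnancy.

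**Does changing the denominator repair miscarriage?** Use Example A with 275 per arm and a pooled two-proportion z.
- Per pregnancy: 110 direct and 137.5 conventional pregnancies. The pooled rate is (16.5 + 27.5) / 247.5 = 0.178, the standard error is √[0.178 × 0.822 × (1/110 + 1/137.5)] = 0.049, and z = 0.05 / 0.049 ≈ 1.0.
- Per participant: the pooled rate is 0.08, the standard error is √(2 × 0.08 × 0.92 / 275) = 0.023, and z = 0.04 / 0.023 ≈ 1.7.

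The misleading signal becomes stronger, because participants who never conceive count as having no miscarriage. The denominator change corrects the direction for ongoing pregnancy but not for miscarriage.

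**Definition against schedule.**

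| Outcome | Evidence required | Scheduled measurement |
|---|---|---|
| Clinical pregnancy | Sac on ultrasound at 6–8 weeks | The 6–8 week scan |
| Ongoing pregnancy | Heartbeat on ultrasound, progress past 6–8 weeks | None; later contacts are by phone |

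**The case against.** Live birth is primary and already counted per participant. In Example A it would show the harm, taking continuing pregnancies as live births. That stands, and it limits the damage. But the article does not rank live birth above the other clinical outcomes, so a favourable per-pregnancy result would be reported as a primary finding.

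Miscarriage per clinical pregnancy is a natural clinical description, and moving to participants does not rescue it as a comparison. This also stands, and it is why the remedy for miscarriage differs from that for ongoing pregnancy.

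An analysis plan that is not shown might settle the denominators. It could not do so without contradicting definitions the article already states.

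Several stronger readings are tempting but not supported.
- **That ongoing pregnancy cannot be measured at all.** A sac and a heartbeat are different findings even at one scan, routine scans are permitted, and the 20–24 week call can establish that a pregnancy continued. What the text shows is that no week is fixed and no scan is scheduled for this outcome.
- **That the bias favours direct warming.** Example B runs the other way, so the direction is unknown.
- **That the smaller denominator costs power.** For an assumed miscarriage difference of 20% vs 10%, power per pregnancy is about 55%, 64% and 72% at clinical pregnancy rates of 40%, 50% and 60%. Per participant it is about 51%, 61% and 69%. The case is about validity, not power.
- **That known failures will be imputed.** A reader might infer this from "Missing data will be handled using multiple imputation to maintain the integrity of the results". But a participant with no surviving embryo or no transfer has a known negative outcome, so nothing is missing, and the text does not say otherwise.

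**Conclusion.** The point holds for both defects. Two of the five primary outcomes have denominators formed after randomisation, which conflicts with the stated intention-to-treat population and with the live birth definition beside them. The definition of ongoing pregnancy also does not match the schedule.

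In the illustration, a 5-point advantage per pregnancy (85% vs 80%) sits beside a 6-point disadvantage per participant (34% vs 40%). The size and direction in the actual trial are unknown, because the article gives no rates. The reversal requires that warming affects the chance of pregnancy, which the article itself treats as possible. The conflict between definition and analysis population does not depend on any assumed rate. The change should be made, but live birth per participant gives the trial one clinical primary outcome that is sound in this respect.

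**What to change.** 1. State clinical pregnancy and ongoing pregnancy per randomised participant, with everyone randomised in the denominator, to match live birth and {20c}.
2. Either define ongoing pregnancy as a heartbeat at the scheduled 6–8 week scan or drop it, so that the definition and Table 1 agree.
3. Remove miscarriage as a stand-alone primary comparison. Report it per clinical pregnancy and per randomised participant as supporting outcomes, read beside live birth per participant.

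**Cost.** Only wording changes, with no new visits. Ongoing pregnancy per participant will be lower than the per-pregnancy figure, and one primary outcome is demoted. Trial status describes the study as preparing for recruitment, but the planned start of 1 November 2025 precedes the article's publication date. If enrolment has begun, the change should be a documented amendment made before anyone sees outcomes by arm.
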